**Methods:**

The intervention was developed based on focus groups with the target group. The cognitive-behavioral 12-module webinar-based group intervention focuses on suicide bereavement-related themes such as feelings of guilt, stigmatization, meaning reconstruction and the relationship to the deceased. Further, the webinar includes testimonial videos and psychoeducation. The suicide survivors are randomized to the intervention or the waiting list in a group-cluster randomized controlled trial. Primary outcomes are suicidality (Beck Scale for Suicide Ideation) and depression (Beck Depression Inventory-II) and secondary outcomes are symptoms of prolonged grief disorder (Inventory of Complicated Grief-German Version ), posttraumatic stress disorder ( Revised Impact of Event Scale ), stigmatization (Stigma of Suicide and Suicide Survivor ) and posttraumatic cognitions (Posttraumatic Cognitions Inventory).

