### Trial design

This study is a randomized control group design with two groups of equal sample size: the treatment group and the waitlist control group. The treatment group will receive treatment through the online group intervention immediately after registration. As a result of the focus groups with suicide survivors, the waitlist control condition was selected as the only one acceptable to the suicide survivors involved. A control that would not receive the intervention after the waiting period could reduce the motivation to participate.

This intervention is based on cognitive behavioral principles (psychoeducation, cognitive restructuring, dealing with difficult emotions such as guilt, shame, suicidality) and will take place once a week over a course of 12 weeks in total. The waitlist control group will receive the same intervention 12 weeks after registration. Participants will be randomly assigned to either group using computer-generated block-randomization. The study protocol was written in accordance with Statement Standard Protocol Items: Recommendations for Interventional Trials (SPIRIT) 2013 [33]; for the SPIRIT Checklist see Additional file 1).

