### Randomization

We will use block randomization without extra stratification: As soon as 10 participants are included, they are considered to form a group. A researcher (first author) who is not involved in participant recruitment, clinical assessments, or treatment, obtains the information by e-mail that a new group is complete. Then, the whole group is randomly assigned to either the treatment or the waitlist control group. The researcher then executes the randomization using a generated list at www.random.org. The person who is allocating the participants thus has no influence on the randomization and enrollment process. Following randomization, participants will be notified of their allocation.

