### Statistical analysis

We will use repeated measures analysis of variance (ANOVA) to analyze the changes in the primary endpoint variables (suicidality and depression) and the secondary outcomes from baseline to post-measurement and the two follow-up assessments (3 months, 6 months), where the dependent variable will be the treatment condition (treatment group vs. waitlist control group). In addition, we will control for the baseline levels of depression and suicidality using analysis of covariance (ANCOVA). The predictor analyses will be conducted using the method of multiple regression. Interim analyses will be calculated to present first results before the study is finished. To control for differences between the online groups, multilevel analyses will be conducted to allow for variation between participants and online groups at level 1. The assignment to the study group (i.e., treatment, wait list) will be on level 2. Intraclass correlation will be tested to examine potential clustering effects of the online groups.

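### Whole online groups are randomised, but the ANOVA and ANCOVA of the primary endpoints have no group term, the multilevel model assigns its levels wrongly as worded, and no analysis is named as decisive; type I error exceeds 5% if outcomes correlate within groups

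*Protocol article*

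**What the plan says.** The abstract's Methods paragraph describes the design: "The suicide survivors are randomized to the intervention or the waiting list in a group-cluster randomized controlled trial". The Randomization section explains that 10 included participants make up a group, and continues: "Then, the whole group is randomly assigned to either the treatment or the waitlist control group". The Sample size section aims for 104 participants, which is about 10 groups, and mentions neither an ICC nor a design effect.

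The Statistical analysis section names repeated measures ANOVA for the primary and secondary outcomes, from baseline to post-measurement and both follow-ups. ANCOVA is to adjust for baseline depression and suicidality. Neither is given a group term. To deal with differences between online groups, the section adds that "multilevel analyses will be conducted to allow for variation between participants and online groups at level 1". It continues: "The assignment to the study group (i.e., treatment, wait list) will be on level 2". Last comes the ICC: "Intraclass correlation will be tested to examine potential clustering effects of the online groups". The section does not rank these analyses.

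**The concern.** When whole groups are randomised, the arm difference has to be judged against the variation between groups. ANOVA and ANCOVA without a group term judge it against the variation between about 100 participants treated as independent. If members of a group resemble each other, the standard error is too small, in the direction that favours a positive claim. Some resemblance is plausible in the treated arm: members share 12 weekly sessions and the same two leaders, and the Introduction counts group cohesiveness and interpersonal learning among the therapeutic elements of grief groups.

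The multilevel model is the intended remedy, but its levels are misassigned as worded. With online groups on level 1 beside participants, between-group variance stays in the participant residual. With the arm as the level-2 unit there are two units, and the arm effect cannot be separated from level-2 variance. The arm should be a fixed predictor measured on the group.

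Since no analysis is named as decisive, adjusted and unadjusted results could disagree, and the plan has no rule for which one stands.

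**Working it through.** **Inputs from the protocol article.** Group size 10 (Randomization). Total 104, d = 0.80, power 0.80, two-sided alpha 0.05, dropout 30% (Sample size). Groups: 104/10 ≈ 10, or 5 per arm with equal arms. Completers per group: 0.7 × 10 = 7, or 0.7 × 104/10 = 7.28 if all 104 are spread over 10 groups.

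**Assumed.** ICC from 0 to 0.10, because the document gives none.

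**The plan's own figure.** A two-sample t test at these inputs needs 26 per arm. With dropout, 26/0.7 = 37.1, so 38 per arm, not the stated 52. After dropout 52 leaves 36.4, and 36.4/26 = 1.4. That would match a design effect of 1.4, but the document does not say so. Such an allowance would in any case protect power, not the error rate of an unadjusted test. The 52 is a separate matter.

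**Unadjusted test.** The design effect is DE = 1 + (m − 1) × ICC. The model standard error is 1/√DE of the true one. The true two-sided error at nominal 5% is 2 × [1 − Φ(1.96/√DE)]. If only the treated arm clusters, DE is replaced by (1 + DE)/2.

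Example with m = 10 and ICC 0.05: DE = 1 + 9 × 0.05 = 1.45; 1/√1.45 = 0.83; error 10.4%. With one arm clustered: (1 + 1.45)/2 = 1.225; error 7.7%.

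| ICC (assumed) | m = 10, both arms | m = 7, both arms | m = 10, treated arm only | m = 7, treated arm only |
|---|---|---|---|---|
| 0 | 5.0% | 5.0% | 5.0% | 5.0% |
| 0.01 | 6.1% | 5.7% | 5.5% | 5.4% |
| 0.02 | 7.1% | 6.4% | 6.1% | 5.7% |
| 0.05 | 10.4% | 8.6% | 7.7% | 6.8% |
| 0.10 | 15.5% | 12.1% | 10.4% | 8.6% |

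Simulation (40,000 trials per setting, 5 groups per arm, one score per participant) agrees within half a percentage point. For ICC 0.05 and 0.10 with both arms clustered it gives 10.4% and 15.5% (m = 10), and 8.5% and 12.3% (m = 7). With only the treated arm clustered and m = 10 it gives 7.7% and 10.5%. With two time points, this test equals the time-by-arm test of a repeated measures ANOVA on change scores.

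**Group-level test on the same data.** A t test on group means with 8 df has a simulated error of 4.8–5.3% over these settings.

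**Power of the group-level test.** The variance of a group mean is ICC + (1 − ICC)/m. At ICC 0.05 and m = 7.28 this is 0.05 + 0.95/7.28 = 0.1805. The standard error of the difference is √(2 × 0.1805/5) = 0.269, and 0.80/0.269 = 2.98. With 8 df the power is about 74% (73% at m = 7). At ICC 0 and m = 7 it is 83%.

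**Why the ICC test should not decide.** With 10 groups of 10, that test has 23% power at ICC 0.05 and 47% at 0.10. Adjusting only after a significant test would leave an overall type I error of 8.4% and 9.1%.

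**The case against.** The strongest reply is that clustering is not ignored. The multilevel analyses are planned unconditionally and for the stated purpose of controlling for group differences. The level-2 sentence can be read as making the arm a level-2 predictor, which is correct, and an ICC for online groups presupposes the group as the clustering unit. The model may therefore be sound and only badly worded. This stands in part: a reader might infer that the model cannot be fitted or that the plan overlooks clustering, and the document does not support going that far. But the favourable reading needs the level-1 wording set aside, leaves ANOVA and ANCOVA unadjusted, and does not say which result counts.

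It is also fair that the waitlist arm has no group sessions before the post-treatment assessment, so equal clustering in both arms may overstate the problem. The one-arm columns of the table meet this.

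Three further inferences should not be drawn:

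- That adjustment will be dropped if the ICC is not significant. The document only says that the ICC will be tested.
- That chance could leave the arms badly unequal. The Trial design section states "two groups of equal sample size" and block randomisation; how the list was blocked is detail that an article leaves out.
- That calling the arm the dependent variable ("where the dependent variable will be the treatment condition (treatment group vs. waitlist control group") changes a result. It is a slip, since the same sentence says that changes in the endpoints are analysed.

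**Conclusion.** The point holds in conditional form. Groups are the randomised unit, the ANOVA and ANCOVA of the primary endpoints have no group term, the multilevel model is misassigned as worded, and the deciding analysis is not named. If the ICC is above 0, the ANOVA and ANCOVA standard errors are too small.

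Over an assumed ICC of 0.01 to 0.10 with 5 groups per arm, type I error is about 6–16% (10 per group) or 6–12% (7 completers) when both arms cluster equally, and about 5–10% when only the treated arm does. At ICC 0 it is 5%. A reader might take the inflation as established, or take the ANOVA as the declared main analysis. The document supports neither: it gives no ICC, and the ANOVA's priority can be inferred only from the order of the sentences.

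**What to change.** Name one linear mixed model as the primary analysis of BSS and BDI-II, and settle it before the group codes are revealed:

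- **Time points:** those already set under Primary outcomes (post treatment, 3 and 6 months), with the arm comparison at follow-up only where a control comparison still exists. The Trial design section gives the waitlist the intervention 12 weeks after registration.
- **Levels:** visits within participants, and participants within online group, with a random intercept for online group.
- **Fixed effects:** arm as a group-level independent variable, and the outcome's own baseline as covariate.
- **Inference:** small-sample degrees of freedom based on the number of groups (10 − 2 = 8 in the simple case).
- **ICC:** reported as an estimate. The group term stays whatever the ICC test shows.

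Any ANOVA or ANCOVA that is kept should be labelled secondary and unadjusted for clustering. The wording on the dependent variable should be corrected in the same edit.

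No new data are needed. The cost is wider confidence intervals and lower power: about 74% for d = 0.80 at an assumed ICC of 0.05, with 5 groups per arm and about 7 completers each, against the planned 80%.

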### Handling of missing data

We will follow the principles of intention-to-treat analysis. Participants who drop out of the study after randomization are asked to state their reasons for doing so and are asked to continue the assessments. Missing values will be imputed using the approach of last observation carried forward. In the case of a participant dropping out during the intervention, the participant will be asked to fill in the post-questionnaire, and the reason for dropping out will be assessed.

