### Sample size

We based the power and sample size estimations in the current study on results from previous studies examining the effectiveness of online bereavement interventions [34]. Assuming a between-subject effect size of *d* = 0.80, power of 0.80, alpha of 0.05 (two-sided), and a dropout rate of 30%, the within-group sample size should be at least 52 participants. Hence, we aim to include 104 participants in total.

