During treatment, participants may experience a worsening in mood and sadness at first when they deal with the suicide of their loved ones. Such mood aggravations are normal in an intensive grief process and usually exist only for a short time. In the case of acute suicidality (i.e. corresponding hints in the suicidality item of the BDI-II), we contact the participant by telephone and offer counseling. He or she may be excluded from the program and referred to local professionals. However, the scientific evidence so far suggests that the proposed online program can reduce difficulties in coping with grief reactions and symptoms. Hence, we do not expect any unwanted side effects or lasting psychopathological worsening at the end of the program. Additionally, a supervisor will provide clinical supervision every fourth session to ensure treatment adherence and provide clinical support.

There will be no external data monitoring committee because the Sponsor and cooperation partners will function whereby procedures, results, and modifications have to be communicated on a regular basis (at least twice annually). Although the execution of the study and the data analyses are independent of these institutions, we will write several interim reports about the achievement of project aims, results, and finances and justify deviations. If adverse events arise in the suggested procedures (e.g. eligibility criteria, randomization strategy, parts of the intervention, etc.) the study coordinators will discuss the necessity and impact of possible changes to the study protocol. An audit is not scheduled in our study.

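### Last observation carried forward is the only stated method for missing outcomes; with 30% dropout allowed for and symptoms expected to fall, it biases the treatment effect

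*Protocol article*

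**What the plan says.** Under Handling of missing data, the protocol article commits to intention to treat ("We will follow the principles of intention-to-treat analysis") and then fixes the imputation rule: "Missing values will be imputed using the approach of last observation carried forward". The rule is not limited to particular outcomes, so it covers both primary outcomes, suicidality and depression. No alternative or sensitivity analysis stands beside it.

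The same section tries to limit the loss of data. Participants who drop out after randomization "are asked to continue the assessments", and those who leave during the intervention are asked for the post-treatment questionnaire.

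The Sample size section allows for "a dropout rate of 30"%. Process measures states the expectation that depressive and suicidal symptoms decline over the intervention. Statistical analysis names repeated-measures ANOVA first, then ANCOVA on baseline, then multilevel analyses. The multilevel analyses are there to deal with differences between online groups; nothing says that they take over the handling of missing values.

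**The concern.** Last observation carried forward (LOCF) assumes that a participant's score stays where it was last seen. The protocol expects scores to move. A treated participant who leaves early and gives no later data is recorded as having gained little or nothing. A waitlist participant who is lost has any natural recovery removed. If these losses are equal between arms, the effect is diluted. If they are unequal, the difference in losses itself turns into a difference between arms, and its direction depends on which arm loses more.

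At stake is the size of the reported effect on both primary outcomes and, with unequal dropout, whether a small difference is real at all. LOCF therefore cannot be defended as reliably conservative.

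**Working it through.** **Inputs from the documents.** "Assuming a between-subject effect size of *d* = 0.80"; "power of 0.80, alpha of 0.05 (two-sided), and a dropout rate of 30"%; and "the within-group sample size should be at least 52 participants" (all Sample size).

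**Assumptions, not in the documents.** Dropouts without later data carry their baseline score. The waitlist arm improves naturally by 0.3 to 0.5 SD. Dropout may differ by arm. For the simulation: correlation of 0.6 between baseline and outcome, dropout at random, no clustering.

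**The plan's own figure.** A two-sample t-test with d = 0.80, 80% power and two-sided alpha of 0.05 needs 26 per arm. Then 26 / 0.70 = 37.1, so 38 per arm. The stated 52 per arm is not reproduced. That is a separate matter; 52 is used below only as the planned arm size.

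**Formula.** Let d be the true effect, nat the natural recovery in both arms, and pT and pC the proportions missing in the treatment and waitlist arms. With baseline carried forward,

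LOCF effect = (1 − pT)(nat + d) − (1 − pC) nat.

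Positive values favour the intervention.

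| True d | nat | pT | pC | Calculation | LOCF effect |
|---|---|---|---|---|---|
| 0.80 | any | 0.30 | 0.30 | 0.70 × 0.80 | 0.56 |
| 0.80 | any | 0.15 | 0.15 | 0.85 × 0.80 | 0.68 |
| 0.80 | 0.4 | 0.30 | 0.10 | 0.70 × 1.20 − 0.90 × 0.40 | 0.48 |
| 0 | 0.4 | 0.30 | 0.10 | 0.70 × 0.40 − 0.90 × 0.40 | −0.08 |
| 0 | 0.3 | 0.20 | 0.40 | 0.80 × 0.30 − 0.60 × 0.30 | 0.06 |
| 0 | 0.5 | 0.20 | 0.40 | 0.80 × 0.50 − 0.60 × 0.50 | 0.10 |

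The second row is the case in which half of the 30% still supply their outcome. If instead half of the dropouts carry a mid-treatment score by which half of the change has occurred, the estimate is 0.80 × (0.70 + 0.15 × 0.5) = 0.62.

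**Simulation** (52 per arm, ANCOVA on baseline). With d = 0.80, nat = 0.3 and 30% dropout in each arm:

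| Analysis | Mean effect | Model SE | Coverage of nominal 95% interval |
|---|---|---|---|
| LOCF | 0.56 | 0.154 | 67% |
| Observed data, valid under missing at random | 0.80 | 0.189 | 95% |

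With no true effect and dropout of 20% (treatment) and 40% (waitlist), LOCF shows a false benefit of 0.06 SD (nat = 0.3) to about 0.11 SD (nat = 0.5). The 0.11 reflects rounding to whole participants; the formula gives 0.10. Type I error is about 7% and about 10% respectively.

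**Standard error.** (0.189 − 0.154) / 0.189 = 18.5%, so the LOCF standard error is about 18% below that of the analysis valid under missing at random, because carried values count as observed. The sampling SD of the LOCF estimate itself is 0.135 when the number of dropouts is held fixed and 0.155 when each participant drops out at random. The model SE of 0.154 is not materially below either.

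**The case against.** Several points on the other side have weight.

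- **The amount missing.** A reader might infer that nearly a third of the outcomes will be made up by the rule. The documents do not support that. The 30% is a planning allowance, and dropouts are asked to go on with the assessments. Leaving the program is not the same as losing the outcome. The 0.56 is therefore the upper end of the dilution under equal dropout within the allowance, and 0.68 is a fair figure if half respond.
- **The standard error.** A reader might infer that LOCF understates its standard error and that this explains the poor coverage. It does not. The model SE matches or exceeds the estimator's own sampling SD, so the fall to 67% is bias. The SE is smaller only than that of a different analysis, one that targets the intended effect.
- **The temporary worsening.** The Monitoring section says that "participants may experience a worsening in mood and sadness at first", and it is tempting to say that LOCF would carry that peak forward. This needs a full BSS or BDI-II score during treatment. Process measures names only the PHQ-D depression subscale and one BDI-II item after each session. The instruments at the mid-point assessment are in Table 1, which was not available for this review. The mechanism is possible but not shown, and no figure above rests on it.
- **The expected decline.** The stated expectation concerns the course of the intervention, not people who stopped or who wait. It makes constancy after dropout doubtful; it does not say how dropouts fare.
- **Direction.** With equal dropout and no true effect there is no bias, and type I error is nominal (4.8% in simulation). A false benefit needs heavier loss on the waitlist together with natural recovery, and both are assumptions.

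These points limit the size of the problem. They do not rescue the rule, which stays the only stated method for whatever is missing.

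**Conclusion.** The concern holds as a matter of bias. The protocol fixes a single-imputation rule that sits badly with its own expectation of falling symptoms and its own dropout allowance. If baseline is carried forward, a true d of 0.80 is estimated as 0.56 with 30% missing in each arm, and as about 0.68 with 15% missing. If dropout also differs by arm and symptoms recover naturally, an ineffective intervention can look worse by about 0.08 SD or better by about 0.06 to 0.11 SD. The 30% and the 0.80 come from the protocol. The carried baseline, the natural recovery and the unequal dropout are assumptions, so these figures show a plausible range and are not a forecast.

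**What to change.** Replace LOCF as the primary method. Fit a likelihood-based mixed model to all observed BSS and BDI-II values of all randomised participants, with online group as a random effect. This is valid under missing at random, needs no imputation, and builds on the multilevel analysis already named under Statistical analysis. Keep LOCF at most as a sensitivity analysis. Add one delta-adjusted sensitivity analysis for data missing not at random. Keep the request that dropouts continue the assessments, since it reduces the problem at its source.

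Cost: no new data are needed, but this is more than a change of wording. The mixed model takes the place of the repeated-measures ANOVA as the primary analysis, so that section has to be rewritten. The standard error will be somewhat larger (0.189 against 0.154 in the scenario above), which reflects the information actually observed. With 104 participants in groups of 10 there will be only about ten online groups, so the between-group variance will be imprecisely estimated; that already applies to the planned multilevel analysis. The extra analysis work is modest.

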#### Primary outcomes

The primary outcomes will be the level of suicidality and depression post treatment, and at 3-month and 6-month follow up. Suicidality and depression will be assessed using the following instruments.

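### Last observation carried forward is fixed for every missing value, primary scores included, with 30% dropout planned; it can bias the estimate and its standard error, in a net direction not known in advance

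*Protocol article*

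**What the plan says.** The section Handling of missing data adopts intention to treat and then fixes one method: "Missing values will be imputed using the approach of last observation carried forward". It makes no exception by outcome, visit or reason for missingness. The same section limits the amount of missing data, since participants who leave "are asked to continue the assessments" and those who stop during the intervention are asked for the post-treatment questionnaire.

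The rule reaches the primary endpoint: "The primary outcomes will be the level of suicidality and depression post treatment, and at 3-month and 6-month follow up". The Sample size section allows for substantial loss: "and a dropout rate of 30%, the within-group sample size should be at least 52 participants".

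Two other statements bear on how scores go missing. Under Monitoring, ethical considerations, and safety, a participant with acute suicidality is telephoned and offered counselling, and then: "He or she may be excluded from the program and referred to local professionals". Under Trial design: "The waitlist control group will receive the same intervention 12 weeks after registration". Before T12, then, only the treated arm is in the programme.

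The Statistical analysis section plans repeated-measures ANOVA and ANCOVA, and adds that "multilevel analyses will be conducted to allow for variation between participants and online groups at level 1". Process measures lists only the PHQ-D depression subscale and the BDI-II suicide item after each session. The last full BSS or BDI-II score before T12 is therefore the baseline (T0), or the six-week score (T6) if the full scales are given then. Table 1, which would settle that, is not shown.

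**The concern.** Last observation carried forward (LOCF) rests on the assumption that a person's score stays where it was last measured. That is hard to defend over a 12-week treatment meant to change the score. It also enters the carried value as if it had been observed, so the analysis claims information that it does not have.

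The method is sometimes kept because it is thought conservative. Here that cannot be relied on. For ordinary dropout, carrying an early score forward removes improvement and can shrink a real effect. For a treated participant who leaves because the primary construct got worse, it can put a better score in place of a worse one. Both routes are possible under this protocol, they pull in opposite directions, and their balance is not known before the data are in.

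**Working it through.** **Inputs.** From the Sample size section: 52 per arm, d = 0.80, power 0.80, two-sided alpha 0.05, dropout 30%. Everything else below is an assumption and is marked as such. Results are in SD units with the SD taken as unchanged.

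**1. The plan's own figure.** A two-sample t-test with these inputs needs 26 per arm; 26 / 0.70 = 37.1, so 38 per arm after dropout. The stated 52 is not reproduced (it equals 2 × 26, both arms before dropout). That is a separate matter. I use 52 because it is the planned arm size.

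**2. How many scores the rule may fill.** 0.30 × 52 = 15.6 per arm, or 31.2 of 104, leaving 36.4 measured per arm. This is the upper case, in which no leaver returns T12.

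**3. Ordinary dropout, T0 carried.** Suppose a share p of each arm lacks T12 and would have followed the same course as those who stayed. A trend common to both arms cancels, and the estimated difference is (1 − p) × d.
- p = 0.30: 0.70 × 0.80 = 0.56.
- p = 0.15 (half the leavers return T12): 0.85 × 0.80 = 0.68.
- p = 0: 0.80.

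If leavers would gain only a fraction f of the stayers' benefit, then at p = 0.30 the true effect is 0.80 × (0.70 + 0.30f), while LOCF still gives 0.56. The error is 0.24f: 0.24 at f = 1, 0.12 at f = 0.5, and 0 at f = 0.

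**4. Precision.** Ignoring clustering, a simple comparison that counts all 52 scores per arm has standard error √(2/52) = 0.196. One based on the 36.4 measured has √(2/36.4) = 0.234. Baseline scores carry some information about T12, so the honest figure may lie between these, but LOCF offers no means of reflecting the loss.

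**5. Removal for acute suicidality.** Let k treated participants be removed and lack T12, each with a true T12 score g SD worse than the carried one (k and g assumed). The treated mean is too favourable by k × g / 52.

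| k | g | shift | share of 0.80 | in standard errors (0.196) |
|---|---|---|---|---|
| 1 | 1 | 0.019 | 2.4% | 0.10 |
| 1 | 2 | 0.038 | 4.8% | 0.20 |
| 2 | 1 | 0.038 | 4.8% | 0.20 |
| 2 | 2 | 0.077 | 9.6% | 0.39 |

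The shift is 0 if T12 is collected or the true score is no worse than the carried one.

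**6. Would a better main model cure step 5?** Not by itself. A model using only T0 and T12 places these people near the improved treated mean, so the shift becomes k(g + 0.8)/52. For k = 2 that is 3.6/52 = 0.069 at g = 1 and 5.6/52 = 0.108 at g = 2, both worse than LOCF (0.038 and 0.077). If a session score taken at the crisis has residual correlation r with T12 (assumed), it recovers roughly a share r², leaving k(g + 0.8)(1 − r²)/52:
- g = 2: 0.081, 0.055 and 0.030 for r = 0.5, 0.7 and 0.85.
- g = 1: 0.052, 0.035 and 0.019 for the same r.

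A simulation with regression imputation within the treated arm (T0–T12 correlation 0.6, 52 per arm, 3000 runs) gave 0.061, 0.043 and 0.029 at g = 2, and 0.042, 0.032 and 0.023 at g = 1. With a weak session score the replacement does not reliably beat LOCF on this route. A separate worsened-score analysis is needed.

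**The case against.** The tempting stronger reading is that LOCF here tilts the trial towards treatment, because people who become suicidal under treatment are removed and their healthier earlier scores are carried forward. A reader might infer this from the removal clause together with "During treatment, participants may experience a worsening in mood and sadness at first". The documents do not support it as the main message.

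- It needs a chain of events: acute suicidality, a discretionary removal, a missing T12 although one is requested, no recovery by T12, and a carried score from before the crisis. No rate is given for any of them.
- Removal is from the programme, not from the study.
- The safety section describes the early worsening as usually brief and expects no lasting deterioration. It also provides weekly calls where suicidality is suspected, which makes a missing T12 less likely. Transient sadness is in any case not acute suicidality.
- Acute suicidality and a BDI-II above 35 are entry exclusions, which should keep removals few. The same exclusions do make a carried T0 score a pre-crisis one.
- That the route acts mainly in the treated arm before T12 is an inference, since the assessment table is not shown.

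Two further objections have force. The 0.56 is an upper case: it needs every planned dropout to lack T12 and carry T0, and leavers to do as well as stayers. And sensitivity analyses are commonly left to an analysis plan, so their absence here is no fault.

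What remains is that the protocol does not leave the primary method open. It names LOCF for all missing values, and asking for T12 does not ensure that it is returned.

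**Conclusion.** The concern holds as a general one: a fixed rule, applied to the primary scores with 30% dropout planned, that can bias the estimate and misstate its precision in a net direction that cannot be stated in advance.

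The larger possible error runs against treatment: up to 0.24 SD (0.80 estimated as 0.56), falling towards 0 as more leavers return T12 or as leavers' true benefit falls. The opposite error, through removal for suicidality, is about 0.02 to 0.08 SD for one or two cases with gaps of 1 to 2 SD. The case counts and gaps are assumptions, because the documents give no removal rate. Neither a claim that LOCF is conservative nor a claim that it favours treatment overall is supported. The rule should be changed, but nothing here shows the trial's conclusion to be at risk from the suicidality route alone.

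**What to change.** In Handling of missing data, replace LOCF for the primary outcomes, in both arms, with one of:

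- multiple imputation, followed by the planned ANCOVA or multilevel analysis; or
- a likelihood-based multilevel repeated-measures model that also accounts for online group.

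Use the session PHQ-D depression score and BDI-II suicide item as auxiliary information where available. Add a sensitivity analysis in which participants removed for suicidality with T12 missing receive a worsened score, for example 1 and 2 SD above the carried value. The main model alone does not correct that route. One sentence in the safety section saying that leaving the programme does not end assessments would also help.

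Cost: no new data and somewhat more analysis work. The likelihood option changes the main analysis in the Statistical analysis section, whose multilevel models are there to handle differences between online groups rather than missing visits. Session scores before T12 probably exist only in the treated arm, so the auxiliary information, and hence the imputation models, would differ between arms.
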